### Healthcare economics and utilisation analysis

Resource use items (for example, hospital and hospice bed days, emergency department attendance) will be priced using unit cost schedules such as the NHS Trust financial returns and NHS reference costs[21]. If necessary, finance departments at each of the study centres will be contacted to obtain unit cost information not included in these sources. A within-trial cost-utility analysis will explore the incremental cost per QALY gained by regular early SPC intervention when compared to usual care. QALY will be generated by combining utility information obtained from the EQ-5D and survival data, all collected as part of the trial. Resource use, cost and effect results will be reported as means with standard deviations, with mean differences between the two patient groups reported with 95% confidence intervals. Incremental cost-effectiveness will be calculated by dividing the difference in costs by the difference in effects. Uncertainty around the incremental cost-effectiveness ratio will be explored using non-parametric bootstrapping[22].

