**Control**											
Patient	QLQC-30, LC13, EQ-5D, GHQ-12	X				X			X		
	Telephone interview (QLQC-30, LC13)			X	X		X	X			
Carer	GHQ-12, SF-36, FAMCARE-2	X				X			X		X

EOT = end of trial;EQ-5D = EuroQol-5D;FAMCARE-2 = family satisfaction with advanced cancer care 2; GHQ-12 = General Health Questionnaire-12; LC13 = lung cancer supplement;,QLQ-C30 = Quality of Life Questionnaire Core 30;SF-36 = Short Form 36;SPC = Specialist Palliative Care.

After consent, the following information will be collected from all patients at the baseline assessment prior to randomisation: patient demographics, date and type of diagnostic pleural procedure, histological subtype of mesothelioma, current performance status (from MDT) and co-morbidities, previous treatments and pleural procedures, treatment plan, medication use, patient HRQoL and mood questionnaires (EORTC-QLQC30, EORTC-LC13, EQ-5D, GHQ-12), neutrophil and lymphocyte values at time of diagnosis, International Mesothelioma Interest Group (IMIG) stage of disease[19] at time of diagnosis (staging data will only be collected from selected sites). From the designated main carer, the following information will be obtained: carer current health utilisation, work status (full or part time, retired), HRQoL and mood questionnaires (SF-36, FAMCARE-2, GHQ-12).

At 12 weeks (primary end point) and 24 weeks, patients and carers from both the intervention and control groups will be seen in clinic and the following information will be documented: patient history including recent treatments and hospital/healthcare utilisation, medication use, patient HRQoL and mood questionnaires (EORTC-QLQC30, EORTC-LC13, EQ-5D, GHQ-12). For carers: healthcare resource utilisation, work status (and days of work missed as appropriate), carer HRQoL and mood questionnaires (SF-36, FAMCARE-2, GHQ-12). Clinic visits will ensure better quality, more complete data for the primary endpoint.

Telephone consultations with patients in both the intervention and control group will be performed at 4, 8, 16 and 20 weeks to obtain the following information: recent treatments and hospital usage, medication use, HRQoL questionnaires (EORTC-QLQC30, EORTC-LC13).

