### Clinical outcomes analysis

The primary outcome measure is the transformed global health status subscale score of the QLQ-C30 at 12 weeks from randomisation. Analysis of the primary outcome will be carried out using an analysis of covariance with adjustment for baseline values to compare between groups. Primary and secondary analyses will be carried out on the intention-to-treat (ITT) population.

As a secondary analysis of the primary outcome a mixed-effects regression model will be used, which will account for the repeated measures over time.

Secondary outcomes: for all patient reported secondary outcomes mixed-effects regression models will be used, taking account of the repeated measures. Overall survival from date of randomisation will be analysed using Kaplan-Meir curves and the Log-rank test.

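### The economic analysis describes incremental QALYs as a plain difference in group means, with no adjustment for the EQ-5D collected before randomisation

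*Protocol article*

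**What the plan says.** The section on healthcare economics and utilisation analysis in the protocol article gives the estimator in four steps.

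- Construction: "QALY will be generated by combining utility information obtained from the EQ-5D and survival data, all collected as part of the trial".
- Summary: "Resource use, cost and effect results will be reported as means with standard deviations, with mean differences between the two patient groups reported"; the sentence goes on to promise 95% confidence intervals for those differences.
- Ratio: "Incremental cost-effectiveness will be calculated by dividing the difference in costs by the difference in effects".
- Uncertainty of the ratio: "Uncertainty around the incremental cost-effectiveness ratio will be explored using non-parametric bootstrapping".

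No step names a covariate or a regression.

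The study visit schedule places EQ-5D before randomisation, as part of the baseline set: "patient HRQoL and mood questionnaires (EORTC-QLQC30, EORTC-LC13, EQ-5D, GHQ-12), neutrophil and lymphocyte values at time of diagnosis". It is repeated at two clinic visits: "At 12 weeks (primary end point) and 24 weeks, patients and carers from both the intervention and control groups will be seen in clinic". Table 1 shows no EQ-5D at the telephone contacts. The minimisation factors under randomisation and blinding are centre, chemotherapy plan, performance status and histological subtype. Baseline EQ-5D is not one of them.

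The clinical outcomes section, written at a similar level of detail, adjusts the primary outcome by "analysis of covariance with adjustment for baseline values to compare between groups". For the secondary questionnaires it says "for all patient reported secondary outcomes mixed-effects regression models will be used, taking account of the repeated measures".

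**The concern.** A QALY built as the area under a utility curve contains the baseline utility as its first point. Baseline utility is also correlated with the 12- and 24-week values, so it enters the outcome twice: directly, and through those later values. If the arms differ at baseline by chance, part of that pre-treatment gap appears in the QALY difference. The case for baseline adjustment is therefore at least as strong here as for the 12-week global health score, which the article does adjust. The mixed models for secondary questionnaires do not fill the gap. A QALY is one value per patient, and the economic section does not draw its effect difference from such a model.

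Cost-effectiveness is a stated aim of the trial. Over a short horizon any plausible QALY gain is small, so both a chance shift in the point estimate and an avoidably wide interval matter for the ICER.

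**Working it through.** **No figure to reproduce.** The article states no EQ-5D standard deviation, QALY difference or ICER, so the check measures how far an unadjusted difference is exposed to baseline imbalance.

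**Inputs from the article.** EQ-5D at 0, 12 and 24 weeks; 174 patients allocated 1:1, hence 174/2 = 87 per arm.

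**Assumptions not in the article.** Trapezoidal QALY over 24 weeks; utility SD 0.25 at each time; equal correlation r between time points, taken as 0.25 and 0.5; no deaths or missing values; a true utility gain of 0.05 at both follow-ups for scale. The article's only correlation is 0.25, for the global health score.

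**Weights.** In years: 6/52 = 0.115 at baseline, 12/52 = 0.231 at week 12, 6/52 = 0.115 at week 24.

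**Share of a baseline gap that reaches the QALY difference.** k = 6/52 + r × 18/52.
- r = 0.25: 0.115 + 0.087 = 0.202
- r = 0.5: 0.115 + 0.173 = 0.288

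**Size of a routine chance gap.** SE of the baseline difference = 0.25 × √(2/87) = 0.0379.

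**Shift in the QALY difference from a one-SE gap.** k × 0.0379.
- r = 0.25: 0.0077
- r = 0.5: 0.0109

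**Comparison.** A sustained 0.05 gain is worth 0.05 × 18/52 = 0.0173 QALY. The one-SE shift is 0.0077/0.0173 = 45% of that at r = 0.25, and 0.0109/0.0173 = 63% at r = 0.5.

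**Variance explained by baseline.** With weights in the ratio 1:2:1, the QALY variance is proportional to 6 + 10r and the covariance with baseline to 1 + 3r. The share explained is (1 + 3r)²/(6 + 10r).
- r = 0.25: 1.75²/8.5 = 0.36
- r = 0.5: 2.5²/11 = 0.57

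**Standard error of the QALY difference, 87 per arm.**

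| r | Unadjusted | Adjusted for baseline |
|---|---|---|
| 0.25 | 0.0128 | 0.0102 |
| 0.5 | 0.0145 | 0.0095 |

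**Wider range.** With 78 per arm (the evaluable number in the sample size section), SD 0.20 to 0.30 and r from 0 to 0.7, k runs from 0.115 to 0.358 and the one-SE shift from 0.004 to 0.017 QALY.

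**The case against.** The strongest reply is that the article never calls the difference unadjusted. A mean difference with a confidence interval can come from a regression, and a condensed article may leave covariates to an economic analysis plan that is not shown. This stands in part: the absence of adjustment is the plain reading of the steps, not an explicit statement. But the section sets out the whole route from means to ratio, and the clinical section names baseline adjustment where it is intended. If a separate plan already adjusts, a short clause in this section settles the matter.

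Randomisation also keeps the unadjusted difference unbiased on average, and its sampling variation is reflected in the interval and the bootstrap. That is correct. What remains is conditional bias in the trial actually run, which the bootstrap does not remove from the point estimate, and lost precision. Minimisation on performance status, chemotherapy plan and histology may make the typical baseline gap smaller than the simple standard error used here.

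The no-deaths assumption favours adjustment. The article expects about 6% mortality by 12 weeks, quotes a median survival of 8 to 12 months for the disease, and includes survival in the QALY. Deaths add variance that baseline utility may explain poorly. The 24-week horizon is likewise an assumption, since the section says only that the analysis is within-trial.

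Three stronger readings are tempting, and the article does not support them.
- A reader might infer that uncertainty is given only for the ratio. The same sentence promises 95% confidence intervals for the cost and effect differences.
- A reader might infer that a chance imbalance would overturn the conclusion. A one-SE gap moves the QALY difference by less than the assumed gain. Equalling that gain takes a gap of 0.0173/0.0109 = 1.6 SE at r = 0.5, or 0.0173/0.0077 = 2.3 SE at r = 0.25.
- A reader might infer that the plan will rank bootstrap ratios that change sign. The section says only that uncertainty will be explored by bootstrapping and fixes no interval or display.

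**Conclusion.** The point holds as a weakness in the choice of estimator, not as a contradiction or an error in a stated figure. As described, the QALY difference ignores a baseline measure that the trial collects, that forms part of the outcome and that predicts the rest of it. Part of any chance baseline gap carries over, not all of it: about a fifth to just under a third under the central assumptions. The shift from a routine gap is material beside a modest true gain but smaller than it. The precision given up, 36% to 57% of the QALY variance, is an upper guide because deaths are left out. The direction of the argument does not depend on the assumed SD or correlation, but its size does. The change should be made.

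**What to change.** State in the economic section that incremental QALYs will be estimated by regression of each patient's QALY on arm, baseline EQ-5D utility and the minimisation factors. Use the adjusted arm coefficient, with its 95% confidence interval, as the effect difference in the ICER. Refit the regression in every bootstrap replicate so that the uncertainty matches the point estimate. The group means and standard deviations can still be reported as descriptive results.

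Incremental net benefit or an acceptability curve could be added, but that is an optional choice of presentation.

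The cost is a few sentences in the economic analysis. All the data are already scheduled for collection, and neither the sample size nor any visit changes.

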### Ethics

A favourable ethical approval for this study has been granted by the National Research Ethics Service (NRES) Committee, London (Hampstead), reference 12/LO/0078. The trial will be conducted according to the Declaration of Helsinki[23].

The study intervention is regular early specialist symptom control treatment which will be carried out by SPC teams and is considered to have no additional safety risk compared with usual clinical practice. Despite being an interventional design, the process involved is not novel and is the usual standard of care for these patients, albeit normally provided at a much later stage in the natural history of this illness. This study will simply provide the same care, delivered at an earlier time point.

The key ethical issues are considered to be as follows: no treatments or care will be withheld at any point in the study, with all subjects (in either arm) able to receive any care considered appropriate by the treating physicians. The additional regular SPC input will continue beyond the EOT until death, with remaining subjects integrated into existing palliative care services.

### Dissemination policy

The full trial results will be published in a high impact medical journal; in addition, lay summaries will be developed with public patient involvement members and disseminated through respiratory and cancer charities and support groups. Lay and scientific summaries will be placed on study website http://www.respect-meso.org.

## Discussion

This study will inform clinicians of a potentially novel way to care for patients with this high symptom-burden disease for which there is no cure, and limited treatment options. The additional aspect of healthcare resource utilisation analysis will allow further interpretation of the results and may inform clinicians and policy-makers as to a more complete understanding as to the implications of this intervention.

In the design of the RESPECT-MESO study we have attempted to allow as pragmatic an approach as possible, to ensure as wide as possible external applicability of the results, within the confines of ensuring internal validity and appropriate scientific rigor. One of the central difficult decisions made was to only include subjects with an ECOG PS of 0 to 1. This was based on UK National Lung Cancer Audit data demonstrating approximately 24% mortality at 12 weeks for PS 2 patients with mesothelioma. Such attrition would have significantly increased the challenge of obtaining adequate data for the primary endpoint at 12 weeks. Nevertheless, UK data demonstrate that 70 to 80% of patients with mesothelioma have a PS of 0 to 1 at the time of diagnosis[24–27], so our approach will allow the inclusion of the majority of cases at presentation.

One of the additional key challenges encountered in the setup of the study was developing the necessary links with SPC services. This has been addressed by early engagement with SPC teams and offering SPC team leads the opportunity of taking on local co-principal investigator roles. When screening potential host sites for suitability we have used a feasibility assessment focusing on the availability of SPC services and asking sites to nominate both respiratory and SPC leads for the study.

### Trial status

The study is now open to recruitment at Queen Alexandra Hospital, Portsmouth, the lead centre for the RESPECT-Meso study. Further centres will be opening for recruitment throughout the United Kingdom over 2014/15. Further information can be found at http://www.respect-meso.org.

## Authors’ original submitted files for images

Below are the links to the authors’ original submitted files for images. Authors’ original file for figure 1

## Abbreviations

ANCOVA: analysis of covariance
BLF: British Lung Foundation
ECOG: European Cooperative Oncology Group
EORTC: European Organisation for Research and Treatment of Cancer
EOT: end of trial
EQ-5D: European Quality of Life 5-Dimension questionnaire
ESAS-r: Revised Edmonton Symptom Assessment System
FAMCARE-2: FAMily satisfaction with advanced cancer CARE-2
GCP: Good Clinical Practice
GHQ-12: General Health Questionnaire-12
GHS: global health status
GP: general practitioner
HRQoL: Health Related Quality of Life
ICH: International Conference of Harmonisation
IMIG: International Mesothelioma Interest Group
ITT: intention-to-treat
LC13: lung cancer supplement
LCCNS: lung cancer clinical nurse specialists
MCID: minimal clinically important difference
MDT: multidisciplinary team
MPM: malignant pleural mesothelioma
NHS: National Health Service
NRES: National Research Ethics Service
NSCLC: non-small cell lung cancer
ORTU: Oxford Respiratory Trials Unit
PS: performance score
QALY: Quality-Adjusted-Life-Years
QLQ-C30: Quality of Life questionnaire Core 30
SAE: serious adverse event
SF-36: Short Form 36
SPARC: Sheffield Profile for Assessment and Referral to Care
SPC: specialist palliative care
UK: United Kingdom
US: United States.
